## Abstract

**Background:**

Acquiring a traumatic injury constitutes a severe life change for the survivor, but also for the surrounding family. The paradigm of helping the family has primarily been on psychosocial interventions targeting caregivers. However, interventions including both survivor and caregivers should be an essential part of treatment, as the whole family’s functional level and mental health can be affected. The current study protocol presents a manualized family intervention for families living with traumatic injury to the brain (TBI) or spinal cord (tSCI). The objectives are to investigate if the intervention improves quality of life (QoL) and decreases burden. It is hypothesized that the family intervention improves problem-solving strategies and family dynamics, which will reduce the burden. This may improve the caregivers’ mental health, which will improve the support to the survivor and QoL.

**Methods:**

The study is an interventional, two-arm, randomized controlled trial. During a 2-year period, a total of 132 families will be included. Participants will be recruited from East-Denmark. Inclusion criteria are (1) TBI or tSCI, (2) ≥ 18 years of age, (3) ≥ 6 months to ≤ 2 years since discharge from hospital, (4) ability to understand and read Danish, (5) cognitive abilities that enable participation, and (6) a minimum of one family member actively involved in the survivor’s life. Exclusion criteria are (1) active substance abuse, (2) aphasia, (3) prior neurologic or psychiatric diagnose, and (4) history of violence. Within each disease group, families will be allocated randomly to participate in an intervention or a control group with a ratio 1:1. The intervention groups receive the family intervention consisting of eight sessions of 90 min duration. Families in the control groups receive 2 h of psychoeducation. All participants complete questionnaires on QoL, self-perceived burden, family dynamics, problem-solving strategies, mental health, and resilience at pre-intervention, post-intervention, and 6-month follow up.

**Conclusion:**

If the intervention is found to have effect, the study will contribute with novel knowledge on the use of a manual-based intervention including the entire family. This would be of clinical interest and would help families living with the consequences of TBI or tSCI.

**Trials registration:**

ClinicalTrials.gov, NCT03814876. Retrospectively registered on 24 January 2019.

## Background

### Background and objectives

Each year traumatic injury to the brain (TBI) or spinal cord (tSCI) affects approximately 3000 individuals and their families in Denmark [1, 2]. TBI and tSCI are complex injuries often followed by a broad range of disabilities. Survivors of TBI may experience cognitive, somatic, affective, behavioural, and motor difficulties [3, 4], and survivors of tSCI may experience complete paralysis or motor and sensory difficulties in relation to urinary bladder, bowel management, sexual function, respiratory and cardiovascular function etc. [5]. Acquiring a traumatic injury not only has an impact on the survivor, but will also affect their families, as they will have to adapt to the changed life situation as well [6–8]. The consequences can affect the family early on [9, 10], but also long term [11–13]. Several families report low level of family functioning up to 5 years after injury [14, 15]. Very often the family members must perform a considerable number of tasks related to the patient. About 43% of caregivers for TBI survivors report spending more than 5 h per week helping their injured family member, and of this group, 22% spend more than 16 h each week [11, 12]. In a group of caregivers for patients with tSCI, 39% reported they stopped working to be able to take care of their injured family member [16]. Families with TBI report high frequencies of anxiety and depression symptoms [17, 18], and high emotional burden [7, 13]. Similar results have been found among families living with tSCI [6, 19]. Furthermore, impaired quality of life (QoL) has been reported for both groups [5, 10, 12, 13, 16, 20], for as long as up to 20 years after injury [21]. The reason may be that the family is facing a new life situation for which they are not prepared, as a traumatic injury is sudden and unexpected [22]. Consequently, most families do not have the appropriate coping strategies [23–25]. Thus, it is important to help the family in coping with the changed life situation [26].

So far, the paradigm and focus of helping the family has been psychosocial interventions primarily targeted at caregivers. The assumption behind most interventions has been that the best way to take care of the survivor is to take care of the caregiver. Thus, most interventions have included only the primary caregiver of the close family. Such interventions have consisted of psychoeducation and support [27–30], stress management [18, 31] skill-building and problem-solving strategies [32–35]. These interventions have shown improvement of problem-solving strategies, reduced emotional burden, anxiety and depression for the primary caregiver. However, it is unclear how this type of intervention affects the survivor. As most intervention programmes work with the survivor and caregiver separately, there is a lack of focus on the entire family. Interventions including the whole family should be an essential part of the treatment [36], as the injury can affect the family dynamics, including roles, boundaries, and communication. Both internationally [19, 24, 37–39] and nationally in Denmark [7, 9, 11, 40], negative effects on the family’s functional level and mental and physical health have been well-documented. This can affect the quality of the care that the caregiver provides [8]. By intervening in the functioning of the entire family, it may be possible to influence QoL and the outcome for both the survivor and the caregiver [8]. However, such a relationship has not yet been elucidated longitudinally, and there have been only a few cross-sectional studies [25, 41].

In a pilot study conducted in Latin America [42], the effectiveness of a newly developed eight-session manualized family intervention for individuals with spinal cord injury (SCI) was evaluated. The preliminary results of this pilot study showed large effect sizes in relation to depression, anxiety, stress and problem-solving strategies. Families, who received the intervention, experienced significant improvements in depression and anxiety, and this effect was maintained at 6-month follow up. Furthermore, effects on burden were also found as well as improved problem-solving strategies. Based on these promising pilot results, this current study seeks to investigate the family intervention in a Danish population.

Consequently, the aim of the present study is to investigate the effect of the eight-session manualized family intervention on QoL in individuals with TBI or tSCI and their family members, compared to a control group. The effect will be measured short term (post-intervention) and long term (6-month follow up). It is assumed that people who survive a traumatic injury do so in the context of their family. Therefore, a minimum of one family member, actively involved in the patient’s life, must be included in each session of the intervention. To our knowledge, the present randomized controlled trial (RCT) will be the first to evaluate the effectiveness of a manual-based family intervention to improve QoL in the entire family. This will be investigated by the following primary research question: Will the families in the intervention groups report improved QoL compared to the families in the control groups? The secondary research question is: Will the families in the intervention groups report decreased burden compared to the families in the control groups? It is hypothesized that the family intervention will lead to improved QoL and decreased burden for both the survivor of TBI or tSCI and their caregivers. Consequently, better mental health of the caregiver will improve the care and support they provide to the survivor. This improvement will ultimately improve the QoL of the survivor.

## Methods

### Trial design

This is a two-arm RCT of a manualized family intervention conducted in two different disease groups: (1) patients with TBI and (2) patients with tSCI, participating with a minimum of one family member actively involved in the patient’s life. The duration of the study is from October 2018 to October 2021 with an inclusion period of 2 years. The trial was developed according to the guidelines for Standard Protocol Items: Recommendations for Interventional Trials (SPIRIT) statement [43] (see Additional file 1 and Fig. 1), and will be reported as stated in the Consolidated Standards of Reporting Trials statement for reporting randomized trials of social and psychological interventions (CONSORT-SPI) [44].

**Fig. 1 Fig1:**
[figure not shown]
Standard Protocol Items: Recommendations for Interventional Trials (SPIRIT) table of enrolment, intervention, and assessments

### Participants

The present study has an uptake area covering the eastern part of Denmark including the Region Zealand and Capital Region with a total of almost 46% of all inhabitants in Denmark [45]. Patients from this part of Denmark, who have either TBI (moderate to severe) or tSCI, can be included with a minimum of one family member if meeting the following criteria:
Age ≥ 18 years at time of inclusion in the studyBetween ≥ 6 months and ≤ 2 years since discharge from hospitalAbility to understand and read DanishPatients with TBI must score ≥ 7 on the Rancho Los Amigos Scale at time of inclusion in the study, indicating the resolution of post-traumatic amnesia (PTA)Cognitive abilities that enable participation in a manualized intervention (when in doubt, the patient must have Mini Mental State Examination score ≥ 23)

Family members must meet the following criteria:
Actively involved in the patient’s lifeAge ≥ 18 years at time of inclusion in the studyAbility to understand and read Danish

Patients and family members will be excluded if they meet any of the following criteria:
Active substance abuseSevere aphasiaPrior diagnosis of neurologic or psychiatric disorderHistory of violence in the family

#### Recruitment and informed consent

The research study will be conducted at the Department of Neurorehabilitation, TBI Unit, Rigshospitalet, Denmark. The participants will be recruited from two different clinics in Denmark: one clinic for patients with TBI and one clinic for patients with tSCI. Two project nurses will recruit participants, provide information about the study, randomize, and obtain written informed consent. All family members are informed that they have the right to withdraw their consent at any time during the study period. In the case of withdrawal, the family is asked if data already collected can be included in future analysis.

### Manualized family intervention

In the present study, the manualized intervention “Traumatic Brain Injury (TBI)/Spinal Cord Injury (SCI) Family Intervention” will be used [46]. The whole manual for conducting the intervention has been published by the developers and can be accessed from the online version (doi:10.1310/sci2201-49) of their pilot study in the supplementary material [42].

The intervention was developed for patients with TBI or tSCI and their families with the overall purpose to improve the functioning of the individual and the family. The intervention was based on clinical experience and empirical research and constructed by a neuropsychologist in collaboration with a family therapist and a psychologist specializing in cognitive behavioural therapy [46]. In 2017, the manual was translated into Danish by authors TS and AN, and all questions concerning the intervention and translation process were discussed with the developers.

The intervention consists of a 90-min session once a week for 8 weeks and includes strategies and elements from both couples and family therapy. Session 1 is facilitated by the nurse and all participants (both intervention and control groups) will be supervised, while completing the questionnaires before randomization. Sessions 2–8 will address different topics or special strategies and are facilitated by a trained neuropsychologist. Between each session the participants will complete a homework assignment, a between-session task, where the new strategies can be practiced. The content of the sessions is structured as follows (Table 1) [42].

**Table 1 Tab1:** An overview of the sessions, the content and the frequency for the intervention group

Week	Session (topic)	Topic of discussion	Facilitator
1	Introduction	Information about the study; consent to participation; completion of baseline questionnaires; randomization; The homework assignment is given (90 min)	Nurse. If the family is randomized to the intervention group at the end of the session, the neuropsychologist will present the homework assignment
2	Making meaning	Presentation of the study and the individual sessions; expectations to the participants and the facilitator; making meaning of TBI/tSCI and psychoeducation; the homework assignment is reviewed and a new given; session rating scale (90 min)	Neuropsychologist
3	Shifting focus	The relationship between thoughts, feelings, and behaviour; the homework assignment is reviewed and a new given; session rating scale (90 min)	
4	Managing emotions	Learning to identify signs indicating an escalation of emotions and techniques to handle emotions; strategies for overcoming negative emotions; the homework assignment is reviewed and a new given; session rating scale (90 min)	
5	Communicating effectively	Talk-listening techniques and communication improving strategies; communication danger sings; the homework assignment is reviewed and a new given; session rating scale (90 min)	
6	Finding solutions	From problem-talk to solution-talk; problem-solving strategies; the homework assignment is reviewed and a new given; session rating scale (90 min)	
7	Boundary making	Understanding the importance of boundaries in the family; self-care; healthy family dynamics; the homework assignment is reviewed and a new given; session rating scale (90 min)	
8	Conclusion and farewell	Summary of learned skills; the homework assignment is reviewed; session rating scale; completion of post-intervention questionnaires (the facilitator leaves the room) (90 min)	
34 (6 months after session 8)	Follow up	Completion of the follow-up questionnaires. The families receive the questionnaires in a stamped envelope. The families return the questionnaires to the nurse. They will receive a reminder if they forget to return the questionnaires and a follow up by phone if no answer	Nurse

Each session of the intervention follows the same structure (except for session 1: Introduction). The session begins with a quote relevant for the topic of the session. Afterwards, the homework assignment will be evaluated. A new topic is then presented. New techniques and strategies will be practiced and used in relation to a specific challenge faced by the family. Finally, a new homework assignment will be presented.

The family intervention aims at helping families [46] to (1) share ideas about and experiences of the traumatic injury and to create a greater understanding of each other; (2) elicit misunderstandings about a traumatic injury; (3) change mindsets from negative to more positive aspects of their situation; (4) recognise the influence their thoughts have on their emotions; (5) identify signs that indicate escalation of emotions and to learn strategies to manage their emotions; (6) communicate more effectively; and (7) understand the importance of boundaries in the family and learn to clarify them together [46].

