#### Questionnaires

##### Socio-demographic data

The following information will be collected at baseline (session 1): age, gender, number of years of education, and cause and date of injury. Other socio-demographic characteristics will be collected at all three timepoints, i.e. baseline, post-intervention (8 weeks after baseline) and at 6-month follow up including civil status, family member relationship, duration of relationship, members in the household, employment status, number of weekly hours spent on work or education, comorbidities, medical drug use, social network, and whether they have participated or currently are participating in another therapeutic setting with a psychologist. The patients will also complete questions about rehabilitation, if they still receive support from an occupational or physio therapist, and if they have been hospitalized during the family intervention. Caregivers will complete information on the hours spent on caring/supervising the patient each day.

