##### Primary and secondary outcome

The effect of the family intervention will be measured by self-report questionnaires. The outcome measurements are outlined in Table 2 and will be measured at baseline, post-intervention, and at 6-month follow up (Table 2).

**Table 2 Tab2:** Primary and secondary outcome measures

Domain	Assessment	Test tool (outcome measure)	Administered by
Quality of life (QoL)	Generic QoL	Short Form-36 (SF-36) [9, 10, 52, 53]	All participants
	The patient’s disease-specific QoL	QoL after Brain Injury (Qolibri) [54]	Participants with TBI
		International Spinal Cord Injury QoL Basic Data Set [55]	Participants with tSCI
Self-perceived burden	General burden, isolation, disappointment, emotional involvement, environment	Caregiver Burden Scale (CBS) [12, 56]	Caregivers
	Physical, emotional and financial burden	Self-Perceived Burden Scale (SPB) [57]	Participants with TBI or tSCI
Family dynamic	Flexibility	Family Adaptability and Cohesion Evaluation Scales-IV (FACES-IV) [58]	All participants
	Cohesion		
	Communication		
Problem-solving abilities	Confidence	Problem-Solving Inventory (PSI) [59]	All participants
	Personal control		
	Approach-avoidance		
Mental health	Depression	Patient Health Questionnaire-9 (PHQ-9) [60]	All participants
	Anxiety	Generalized Anxiety Disorder-7 (GAD-7) [61]	
	Satisfaction with life	Satisfaction with Life Scale (SWLS) [62]	
Relationship	Relationship to relatives	Relationship Assessment Scale (RAS) [63–65]	All participants if a dyad
Resilience	Resilience and robustness	The Resilience Scale for Adults (RSA) [66]	All participants

All participants in the two groups will complete self-report questionnaires to collect generic QoL data as the primary outcome measurement, and self-perceived burden, family dynamics, problem-solving strategies, mental health, and resilience as secondary outcome measurements. In cases where the family consists of a dyad, e.g. a married couple, mother and daughter etc., rather than several family members, the Relationship Assessment Scale (RAS) [63–65] will be completed as a supplement.

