#### Implementation and awareness of assignment

The project nurses will be responsible for identifying and recruiting families that meet the inclusion criteria. The random allocation sequence will be generated by the nurses using the online randomization procedure [71]. Families will complete the baseline questionnaires before randomization.

Because of the nature of the study, it will be clear to all participants and the neuropsychologist whether the families are allocated to the intervention group or the control group. It is not possible to blind the participants or the neuropsychologist to the group allocation. The nurses will collect the study data. The neuropsychologist and statistician performing the data analyses will not be involved in collection of data on the outcome measures. Thus, they will be blinded to the association between the data from the questionnaires and the group to which the families are allocated. The nurses who are responsible for the data collection will not participate in data analysis.

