### Interpretation

For families allocated to the intervention group, there can be some benefits and harms to consider. Participating in the family intervention may be costly for some families in terms of resources and time rather than an opportunity to receive support and help. This may influence the willingness to participate in the 8-week intervention, as participation may seem too time-consuming. To minimize the burden for the families, the neuropsychologist and nurses will be flexible in scheduling the sessions and the location of the intervention, e.g. if the family members have work or study obligations, then it will be possible to schedule a late session, and if the patient suffers from severe fatigue, then the intervention can be offered at home. Furthermore, the families can have transport expenses reimbursed and the intervention is free of charge.

For families allocated to the control group, there can be some ethical considerations. All families are carefully informed about the study design prior to inclusion, including the information that the randomization to either the intervention group or the control group is 50:50. However, it is possible that families who are willing to participate in the project hope to be allocated to the intervention group. In the worst case, families allocated to the control group may feel rejected, as they had high hopes of receiving help and support. This may harm the family and make them withdraw their consent and quit the project. However, the families allocated to the control group will be offered one psychoeducational session with a neuropsychologist.

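### The intervention arm's post-intervention questionnaires are tied to session 8, an occasion that controls and families who stop early do not have

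*Protocol article*

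**What the plan says.** Under Manualized family intervention, sessions 2 to 8 are led by a neuropsychologist. Table 1, captioned "An overview of the sessions, the content and the frequency for the intervention group", lists in its session 8 row, the closing farewell session, "completion of post-intervention questionnaires (the facilitator leaves the room". The follow-up row is dated "34 (6 months after session 8". It describes a stamped envelope returned to the nurse, with a reminder and then a phone call. No such process is described at session 8.

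Other sections bear on the same assessment:

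- Socio-demographic data gives the time points as "baseline, post-intervention (8 weeks after baseline) and at 6-month follow up", without distinguishing the arms.
- Primary and secondary outcome says the outcomes "will be measured at baseline, post-intervention, and at 6-month follow up" and that "All participants in the two groups will complete self-report questionnaires".
- Implementation and awareness of assignment says "The nurses will collect the study data" and keeps the neuropsychologist out of outcome data collection.
- Interpretation says "the neuropsychologist and nurses will be flexible in scheduling the sessions and the location of the intervention".
- Control group describes a single 2-hour session at some point in the first 8 weeks, with a different neuropsychologist and no assessment attached.
- Analytical methods plans intention-to-treat analyses. Limitations and generalizability expects that the demands of the programme may cause drop-out in the intervention arm.

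**The concern.** An outcome assessment in a randomised trial should be triggered by something both arms share, normally time since randomisation. Here the intervention arm's trigger is attendance at the last treatment session, which follows randomisation and depends on adherence.

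Three things are at stake. First, families who leave the programme are those least likely to reach the occasion on which the outcome is recorded, so missingness may be related to adherence and to outcome. Second, intervention families fill in unblinded self-report forms at the end of a farewell meeting with their therapist, and controls have no comparable occasion. Third, a date counted from session 8 has no meaning for a control family or for a family that never gets there.

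**Working it through.** The plan states no figure on this point, so the main check sets the sections side by side. The arithmetic after that only shows the scale.

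**1. Route.** For the post-intervention assessment in the intervention arm, the only route described is session 8. Envelope, reminder and phone call appear only in the 6-month row. The withdrawal text under Recruitment and informed consent covers the use of data already collected and does not mention collection after a family stops attending. For controls, no place or route is given for this time point.

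**2. Setting.** Baseline is the same in both arms: session 1, supervised by the nurse, before randomisation. At post-intervention, one arm is assessed within a therapist's closing session. The other arm has no such session, wherever its forms are completed.

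**3. Timing.** Two anchors are in use, session 8 and 8 weeks after baseline.

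- With weekly sessions and session 1 in week 1, session 8 falls 8 − 1 = 7 weeks after baseline. The difference from 8 weeks is at most about one week and may be only a counting convention.
- Follow-up: 34 − 8 = 26 weeks, consistent with 6 months.
- So the anchors agree nominally for a family on schedule. They separate if sessions slip, which flexible scheduling makes possible.

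**4. Who collects.** The text assigns collection to nurses. No nurse is listed for session 8, which the neuropsychologist leads.

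**5. Scale of possible bias.** Let p be the share of the intervention arm missing and g the finisher mean minus the non-finisher mean. The full-arm mean is (1 − p) × finisher mean + p × non-finisher mean, so the finisher mean exceeds it by p × g. The 5-point target, SD 12.5 and 10% drop-out allowance come from Sample size. The 20% and 30% loss rates and all values of g are assumptions.

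- p = 0.10: g = 5 gives 0.5 points; g = 10 gives 1.0. Against the target, 0.5/5 = 10% and 1.0/5 = 20%. In SD units, 0.5/12.5 = 0.04 and 1.0/12.5 = 0.08.
- p = 0.20: g = 5 gives 1.0; g = 10 gives 2.0.
- p = 0.30: g = 5 gives 1.5; g = 10 gives 3.0.

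These values assume no loss in controls. With loss in both arms, the bias in the comparison is p × g in the intervention arm minus p × g in the control arm.

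**6. Scale of lost precision.** Splitting the stated 182 per disease group evenly gives 91 per arm. With a difference of 5, SD 12.5, two-sided 5% and clustering ignored, power is 0.770. If 10%, 20% or 30% of the intervention arm alone is missing, it falls to 0.747, 0.720 or 0.687. Loss comes by family: 400 participants / 132 families is about 3 participants each.

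**The case against.** The strongest reply is that Table 1 describes the course of a family that attends as planned. What happens after a missed session is the kind of detail an article leaves to the full protocol, and the SPIRIT schedule in Fig. 1 is not reproduced in the text at hand. The article says all participants in both groups complete the questionnaires and gives one nominal time without distinguishing the arms. The facilitator leaves the room, which fits the statement that the neuropsychologist does not collect outcomes. The examples of flexibility are a late appointment and home delivery, not a longer programme.

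Much of this stands, and it rules out several stronger readings that a reader might infer:

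- That families who stop are not assessed. The text never says so, and nothing excludes them from the 6-month mailing.
- That the arms are measured at different times by design. The nominal time is common; drift is a possibility, not a plan.
- That every effect favours the intervention. A timing shift has no fixed direction, and the article foresees drop-out among controls as well.
- That missing data contradict intention to treat. They make that analysis harder, but analysis by allocation is still planned.
- That the neuropsychologist handles the forms. Nothing says so.

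The reply does not remove what Table 1 positively fixes: an attendance-based occasion for one arm, and a follow-up anchor that the other arm lacks. The common 8-week time is one side of the inconsistency and does not resolve it.

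**Conclusion.** The point holds in limited form and should be corrected. The collection arrangement for the post-intervention outcome depends on attendance in the intervention arm, its setting cannot be matched in controls, and the session 8 anchor is undefined for controls and early leavers. Table 1 therefore sits poorly with the baseline-based timing, with collection by nurses and with the intention-to-treat plan.

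The result is a risk of adherence-related missing data, not a demonstrated loss. Its size cannot be known from the documents. The range of 0.5 to 1.0 points rests on applying the overall 10% allowance to the intervention arm alone, on an assumed gap of 5 to 10 points, and on no offsetting loss in controls. Similar loss in controls could cancel some or all of it; heavier loss in the intervention arm would enlarge it.

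**What to change.** - Date both follow-ups from baseline, which is also the day of randomisation under Table 1, in both arms. Keep the nominal 8 and 34 weeks, state how weeks are counted, and give one common window.
- Have the project nurses collect both assessments by the same route in both arms, whether or not sessions are attended. State that stopping sessions does not end follow-up unless consent is withdrawn.
- Use the 6-month reminder and phone process at 8 weeks too.
- Take the questionnaires out of session 8, and reconcile Table 1 with Socio-demographic data and with Implementation and awareness of assignment.

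Whether the common route is postal or nurse-supervised can be left to the investigators. Supervision would match baseline and may suit participants with cognitive difficulties.

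The cost is wording changes, a little extra nurse work and possibly a slightly lower return than in-session completion, which the reminders should limit. At the reported status 13 of the 132 planned families had been randomised, so the change would reach most of the trial.
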